### Outcomes

The primary outcome is weight change (in kilogram) during and following the treatment for hyperthyroidism, as well as prevalence of obesity following the treatment. The secondary outcomes include cardiometabolic events and mortality as presented in table 1.

**Table 1 T1:** Secondary outcomes and their data sources

Secondary outcome	Source
MACE (cardiovascular death, nonfatal myocardial infarction or non-fatal stroke)	HES
Type 2 diabetes mellitus	CPRD
Congestive heart failure	HES
Ischaemic heart disease	HES
Stroke and transient ischaemic attack	HES
Cardiovascular mortality	ONS
All-cause mortality	ONS

CPRD, Clinical Practice Research Database; HES, Health Episode Statistics; MACE, major adverse cardiovascular event; ONS, Office for National Statistics.

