**Methods and analysis:**

The study will establish the natural history of weight change in hyperthyroidism, investigate the risk of obesity and risks of cardiometabolic conditions and death relative to the treatment. The data on patients diagnosed with hyperthyroidism between 1 January 1996 and 31 December 2015 will come from Clinical Practice Research Datalink linked to Hospital Episode Statistics and Office of National Statistics Death Registry. The weight changes will be modelled using a flexible joint modelling, accounting for mortality. Obesity prevalence in the general population will be sourced from Health Survey for England and compared with the post-treatment prevalence of obesity in patients with hyperthyroidism. The incidence and time-to-event of major adverse cardiovascular events, other cardiometabolic outcomes and mortality will be compared between the treatments using the inverse propensity weighting model. Incidence rate ratios of outcomes will be modelled with Poisson regression. Time to event will be analysed using Cox proportional hazards model. A competing risks approach will be adopted to estimate comparative incidences to allow for the impact of mortality.

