### Data sources

CPRD collects and anonymises patient electronic health record data from a network of general practitioner (GP) practices across the UK.^19^ Although the records in the database cover all four UK countries, HES-linkable records are limited to those from England only. Two HES datasets will be used: HES outpatient and HES admitted patient care. Linkage to HES databases is required to obtain the data, which may be missing from the GP records on non-medical treatment for hyperthyroidism (radioactive iodine and thyroidectomy). Additionally, data on MACEs will also be sourced from HES, as such events are typically being treated in the hospital setting.

Linkage to social data is required to adjust the analysis for socioeconomic status, which is a known risk factor for obesity and increased mortality. This will be obtained as the Index of Multiple Deprivation (IMD). Linkage to Office of National Statistics data is required to get access to the date of death and cause of death. Prevalence of post-treatment obesity will be compared with the background population sourced from Health Survey for England, a yearly survey monitoring trends in the nation’s health and care.

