Proposed time-varying adjustments for both analyses will include postindex date data, that is, treatment with levothyroxine for developed hypothyroidism, logTSH levels and informative observations of number of GP visits in a unit of time. To allow for the fact that patients may die, a competing risks approach will be adopted for estimating comparative incidences for non-fatal events to allow for the impact of mortality as a competing risk.^22^

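### MACE includes cardiovascular death but is given HES as its only source, although the protocol takes date and cause of death from ONS

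*Protocol article*

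**What the plan says.** Outcomes, Table 1, lists seven secondary outcomes with a source for each. The first is "MACE (cardiovascular death, nonfatal myocardial infarction or non-fatal stroke"), with HES in the source column. Further down, "Cardiovascular mortality" is an outcome in its own right, and its source is ONS, as it is for all-cause mortality.

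The Data sources section explains the choice for the composite: "data on MACEs will also be sourced from HES, as such events are typically being treated in the hospital setting". It names the HES files: "Two HES datasets will be used: HES outpatient and HES admitted patient care". Its next paragraph turns to deaths: "Linkage to Office of National Statistics data is required to get access to the date of death and cause of death".

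The abstract (Methods and analysis) confirms that the cohort comes from "Clinical Practice Research Datalink linked to Hospital Episode Statistics and Office of National Statistics Death Registry". The study will therefore hold the death data.

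The section on cardiometabolic risks and mortality deals with death during follow-up: "a competing risks approach will be adopted for estimating comparative incidences for non-fatal events". It does not mention how the fatal part of MACE is ascertained.

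**The concern.** One event, cardiovascular death, has two sources in one table: HES inside the composite and ONS as a separate outcome. The reason given for HES fits a myocardial infarction or stroke that the patient survives long enough to be admitted. It does not fit a death with no hospital contact, and the protocol itself points to ONS for cause of death.

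MACE is the first secondary outcome listed and is compared across three treatments with propensity weighting. If an analyst derives it from HES as the table directs, some patients whose first event is a cardiovascular death will not be counted. The composite would then be partly incomplete in its fatal component and could disagree with the cardiovascular-mortality results in the same report.

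**Working it through.** The protocol states no event rate, event count or sample size for MACE, so there is no figure to reproduce. The check compares the statements and then follows the rule through.

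**Step 1. Sources, side by side.**

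| Item | Where stated | Source named |
|---|---|---|
| MACE, including cardiovascular death | Outcomes, Table 1 | HES |
| MACE | Data sources | HES |
| Cardiovascular mortality | Outcomes, Table 1 | ONS |
| Date and cause of death | Data sources | ONS |

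The first and third rows assign different sources to the same event. No other part of the protocol joins them: none says that ONS deaths are added to MACE, and none says that they are left out.

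**Step 2. What HES can supply.** The two files are outpatient records and admitted patient care. Both record hospital contacts, so a death without such a contact cannot be found in either. For deaths during a hospital stay, the protocol does not describe what HES records, so nothing can be concluded about them.

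**Step 3. Logical relation between the two outcomes.** By the definition in Table 1, a cardiovascular death is itself a MACE. Every patient with a cardiovascular death must therefore have a MACE, at the date of death or before. With MACE from HES and cardiovascular mortality from ONS, this need not hold. A patient with no earlier infarction or stroke who dies of a cardiovascular cause outside hospital would be an event in the mortality analysis. In the MACE analysis the same patient would be censored or counted as a competing death.

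**Step 4. Size, by assumption only.** Let f be the share of first MACE that are cardiovascular deaths and c the share of those deaths identifiable in HES. The share of composite events lost is f × (1 − c). The protocol gives neither f nor c; all values below are assumed.

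| f | c = 0 | c = 0.5 | c = 1 |
|---|---|---|---|
| 0.20 | 0.20 × 1 = 20% | 0.20 × 0.5 = 10% | 0.20 × 0 = 0% |
| 0.40 | 0.40 × 1 = 40% | 0.40 × 0.5 = 20% | 0.40 × 0 = 0% |

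The table shows only how the loss depends on two unknown quantities. It is not an estimate for this cohort.

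**Step 5. Comparison between treatment groups.** The share of events retained in a group is 1 − f × (1 − c). If that share is the same in all groups, it approximately cancels in a rate ratio, and the main cost is precision. If it differs, the ratio shifts by the quotient of the retained shares. The protocol gives nothing from which to judge which case applies.

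**The case against.** The strongest reply is that the table cell is simply incomplete. Cardiovascular death is named as a component, ONS linkage covers the cohort, and the ONS sentence is not restricted to the mortality outcomes. The Data sources sentence can be read as explaining why HES is needed, not as ruling out other sources. The investigators may well intend to use ONS. This stands as a view of intent, but it does not remove the conflict: the table gives one source, the text gives the same one with a reason, and nothing tells the analyst to add ONS deaths.

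A reader might infer several stronger conclusions that the protocol does not support:

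- **That cardiovascular deaths drop out of the composite altogether.** Only deaths not captured in HES are at risk. The protocol does not show that deaths in hospital would be lost or would lack a usable cause.
- **That a definite fraction of MACE is lost.** Any percentage rests wholly on assumed inputs, and zero loss is among the possibilities.
- **That the treatment comparison is biased**, for instance because radioiodine patients may be older. The protocol gives no ages by group, and age at the index date is among the covariates proposed for the propensity model. Bias is possible but not shown.
- **That MACE and cardiovascular mortality are left unprotected against non-cardiovascular death**, because the competing-risks sentence speaks of non-fatal events. The abstract describes the approach without that limit, and a Cox model that censors non-cardiovascular death estimates a legitimate cause-specific hazard. At most the two sentences could be aligned.

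It also counts for the other side that MACE is one of seven secondary outcomes, and that cardiovascular and all-cause mortality are analysed separately from ONS. The deaths are not lost to the study.

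**Conclusion.** The inconsistency is real and is visible within Table 1. Followed literally, the stated rule would miss cardiovascular deaths not captured in HES, notably those outside hospital, and would let the MACE and cardiovascular-mortality outcomes count different deaths. This conclusion needs only the stated definition, the stated sources and the fact that a death without hospital contact leaves no HES record.

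The size of the loss, and whether it differs between treatment groups, cannot be derived from the protocol. The 0% to 40% range reflects the assumed values of f and c and nothing else. The point concerns how a secondary outcome is ascertained. It does not touch the primary outcome of weight change and obesity. It should be settled before outcomes are derived, because it decides which patients count as having a MACE.

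**What to change.** In Outcomes, Table 1, give the MACE source by component: HES for non-fatal myocardial infarction and non-fatal stroke, and ONS for the date and cause of cardiovascular death. Amend the Data sources sentence on MACE to match. State that the fatal component uses the same definition of cardiovascular death as the separate cardiovascular-mortality outcome, so that every such death is also a MACE unless the patient has already had one.

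The cost is one table cell and a sentence or two. No new data are needed, because the ONS linkage is already planned.

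### Ischaemic heart disease, heart failure and stroke/TIA are sourced from HES while death, not split by cause, competes, so a first event fatal before any hospital contact is missed although linked cause of death is available

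*Protocol article*

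**What the plan says.** Three parts of the protocol article bear on this.

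- **Outcomes, Table 1.** Every secondary outcome has a stated source. Three disease rows name HES and nothing else: "Congestive heart failure HES", "Ischaemic heart disease HES" and "Stroke and transient ischaemic attack HES". ONS appears only in the two mortality rows, for example "Cardiovascular mortality ONS". The MACE row calls its infarction and stroke components non-fatal; the three disease rows, such as "Stroke and transient ischaemic attack", carry no such label.
- **Data sources.** HES here means two files: "Two HES datasets will be used: HES outpatient and HES admitted patient care". The same section explains the ONS link: "Linkage to Office of National Statistics data is required to get access to the date of death and cause of death".
- **Cardiometabolic risks and mortality.** A competing-risks approach is adopted "for estimating comparative incidences for non-fatal events to allow for the impact of mortality as a competing risk". Deaths are not divided by cause.

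Nowhere does the article say that a death certified as due to coronary disease, heart failure or stroke counts as an event for that outcome.

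**The concern.** The secondary objective is the effect of treatment on the incidence of cardiometabolic outcomes. A patient whose first stroke or coronary event is fatal before reaching hospital has no record of it in either HES file. Under the stated sources that patient does not have the outcome. Under the competing-risk step the death counts as an event that prevented the outcome, although the disease in question caused it.

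The most severe first events are therefore the ones that go uncounted. At stake are the level of disease-specific incidence, which the study wants to report to patients and clinicians, and, under a further condition set out in the working, the comparison between treatments. The pooled cardiovascular mortality row cannot restore the missing events, because it does not separate coronary, stroke and heart failure deaths.

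**Working it through.** The article states no event rate, event count, sample size or power for these outcomes, so there is no figure of its own to reproduce. The check has two parts: tracing how the rules classify a patient, and showing what follows for assumed values of the unknown share.

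**Step 1: classification under the stated rules.** Take two patients with the same fatal first stroke and no earlier hospital record of the disease.

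| Patient | HES record | Stroke/TIA outcome | Competing-risk step | Mortality outcomes |
|---|---|---|---|---|
| Dies after admission | yes | event | event comes first | counted |
| Dies before any hospital contact | no | no event | competing death | counted |

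The two differ only in whether hospital was reached. The same holds for ischaemic heart disease and heart failure.

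**Step 2: effect on incidence.** Let f be the share of all first events that are fatal without a hospital record. The article does not give f, so 5% to 30% is an assumption. The missed patient leaves follow-up on the date of death whether or not the event is counted, so person-time is unchanged and the observed rate is (1 − f) times the true rate. Adding the ONS deaths raises the event count by the factor 1/(1 − f).

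To show the loss of precision, suppose 631 events with full capture, two equal groups and a hazard ratio of 0.80, which gives 80% power by Schoenfeld's formula at two-sided 5%. These values are illustrative and do not come from the article.

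| Assumed f | Captured, 1 − f | 1/(1 − f) | Illustrative power |
|---|---|---|---|
| 5% | 95% | 1.05 | 78% |
| 10% | 90% | 1.11 | 76% |
| 20% | 80% | 1.25 | 71% |
| 30% | 70% | 1.43 | 65% |

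**Step 3: effect on the treatment ratio.** With a true rate ratio of 1.00, the observed ratio is (1 − f in the comparison arm)/(1 − f in the reference arm).

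| f reference | f comparison | Observed ratio |
|---|---|---|
| equal | equal | 1.00 |
| 5% | 10% | 0.90/0.95 = 0.95 |
| 10% | 20% | 0.80/0.90 = 0.89 |
| 15% | 25% | 0.75/0.85 = 0.88 |
| 10% | 30% | 0.70/0.90 = 0.78 |
| 20% | 10% | 0.90/0.80 = 1.13 |

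Bias in the ratio needs a difference in f between arms, and its direction follows that difference.

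**The case against.** The strongest reply is that the competing-risk sentence limits itself to non-fatal events. If the target is non-fatal disease, death from any cause properly competes, because no non-fatal event can follow it. That is a coherent estimand, but the outcome rows do not implement it. They are not labelled non-fatal, and HES would still count a patient who is admitted and then dies of the same event.

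Several other points stand and limit the concern.

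- The deaths are not lost to the study. They count in cardiovascular and all-cause mortality, so an excess of out-of-hospital cardiovascular death in one arm could show there, though not by disease.
- The article does not say in so many words that HES is the sole source or that deaths from the index disease compete. Both follow from taking Table 1 and the undivided word mortality as written. The full approved protocol, which is not shown, may settle the matter. The issue here is the source the table states, not missing code lists.
- One f does not fit all three rows. A transient ischaemic attack is not fatal, which lowers f for that combined row. Ischaemic heart disease and heart failure are diseases that an earlier outpatient or inpatient record may already have captured.

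A reader might also infer that a treatment followed by more fatal first events would look protective. The documents do not support that as a general statement. It requires f to differ between arms, and it also depends on total incidence: an arm with more events overall could still show a raised ratio in HES. The article gives no data on either, and no reason to expect f to be equal or unequal in this non-randomised comparison.

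**Conclusion.** The concern holds as a matter of outcome definition. Followed as written, the rules classify the same fatal first event differently according to whether the patient reached hospital, and the linked data that would resolve this are used only for the mortality rows.

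Disease-specific incidence is understated by f, hence by 5% to 30% if that range is assumed. The between-treatment ratio is biased only if f differs by arm; 0.88 at 15% versus 25% and 0.78 at 10% versus 30% are conditional illustrations, not estimates. With equal f the ratio is unbiased and the cost is precision. The outcomes are secondary and the size cannot be derived from the article, so this is an inexpensive improvement that should be made, not a flaw that undermines the study.

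**What to change.** In Table 1, define ischaemic heart disease, heart failure and stroke/TIA each as the earlier of the first HES record and an ONS death with that disease as underlying cause, the latter dated at death. In the section on cardiometabolic risks and mortality, state that for each of these outcomes only deaths from other causes compete.

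If hospital-recorded disease is the intended target, label the three rows so and report the ONS-augmented definition as a sensitivity analysis. Comparing the two event counts by treatment arm would also show directly whether f differs.

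The cost is an edit to the table, one sentence in the analysis section and a cause-of-death code list per outcome. No new linkage is needed. The downside is some error in certified cause of death, which the study already accepts for cardiovascular mortality.

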### Confounding

Based on the literature and clinical experience, we identified a number of confounders affecting both the exposure and the outcomes of our study. The modelled outcomes will be adjusted for baseline data (sex, age, IMD quartiles, smoking status and comorbidities) and time-varying covariates (thyroid function, cumulative time on the medical treatment, time since diagnosis, levothyroxine replacement, pregnancy and diagnosis of cancer). Table 2 presents the details of how covariates are defined and handled. Figure 1 depicts the directed acyclic graphs representing the relationship between the covariates. We will explore the relationships between the potential confounders and both exposures and outcomes independently in order to establish their potential role in this particular dataset.

**Table 2 T2:** Definitions of study covariates

Variable	Definition
Aetiology of hyperthyroidism	Identified based on Read codes and categorised in (1) Graves’ disease, (2) toxic nodular goitre and (3) undefined. The undefined category will consist of unspecified diagnosis and missing aetiology data.
Age	Age at index date
Baseline fT4	The highest measurement between 3 months prior to diagnosis and the index date
BMI	Normal (or underweight) <25 kg/m^2^, overweight 25–30 kg/m^2^ and obese ≥30 kg/m^2^; additionally, BMI status will be deduced from the Read code
Cancer diagnosis	Switch-type binary variable assuming lifelong status of cancer comorbidity
Frequency of GP visits	Time-varying variable of number of GP visits in a unit of time
IMD	IMD will be stratified into quintiles.
Levothyroxine (LT4) replacement	Switch-type binary variable assuming lifelong LT4 administration following development of hypothyroidism in radioiodine and thyroidectomy treatment groups
Pregnancy	Time-varying binary variable recording pregnancy
Pretreatment ATD	Cumulative time on ATD between diagnosis and the index date
Sex	Binary variable
Smoking status	As recorded at the index date, last observation carried forward if not available at the index date
TSH	Serial TSH, log-transformed for the analysis
Time since diagnosis	Time-varying variable measuring cumulative time since diagnosis

ATD, antithyroid drug; BMI, body mass index; GP, general practitioner; IMD, Index of Multiple Deprivation; TSH, thyroid-stimulating hormone.

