Prior to diagnosis, the majority of patients with hyperthyroidism notice that they lose weight, often despite increased appetite, due to the regulatory effects of thyroid hormones on metabolism. As thyroid hormone levels normalise following treatment, weight change may be observed. While weight gain following treatment is common, it may become a major psychological stressor and can affect treatment compliance. Untreated hyperthyroidism may result in serious consequences, including thyroid storm, heart failure, embolic events, atrial fibrillation, osteoporosis, muscle weakness, neuropsychiatric symptoms and, rarely, cardiovascular collapse and death.^12^ Patients need to be appropriately counselled about the possibility of significant weight gain associated with the treatment of hyperthyroidism. However, there are currently insufficient data available about weight overshoot, cardiovascular risk and treatment modality selection to provide clear guidance to our patients. In our recent survey of British Thyroid Association members, of 35 clinicians who responded, only 23% usually discuss weight gain with patients treated for hyperthyroidism despite 70% of respondents feeling this was a significant clinical problem.

We recently surveyed doctors and dieticians and found that while there was agreement that weight gain following treatment for hyperthyroidism represents a medical problem, there is no consensus about the significance of or the approach to this anticipated weight gain. When surveyed, dieticians expressed concerns that they are not equipped to advise on dietary issues, given the switch from a highly catabolic state (weight loss state) in untreated hyperthyroidism to a situation of anticipated weight gain following treatment.

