### Data analysis

#### Natural history of weight changes

Descriptive statistics will provide summaries about the sample and weight as the outcome measure.

The natural history of weight changes will be modelled longitudinally. The model will estimate the weight (kilogram) over three stages: premorbid, duration of treatment and post-treatment. Premorbid weight is defined as body weight recorded at least 3 months before diagnosis or treatment initiation (whichever comes first). The treatment phase will start from the time of diagnosis or the first prescribed dose or procedure and will last until 3 months after the last recorded date of treatment. Any weight recoded thereafter will be considered as post-treatment.

Only patients having at least one weight record (quantitative or qualitative) in each of the three phases of the condition (premorbid, treatment and post-treatment) will be included in the natural history of weight analysis. The extent of missing data will be reported. As with any real-world data, we anticipate a relatively high proportion of intermittent missing weight data. This missingness can be assumed to be missing at random conditional on other covariates.^20^ Hence, the missing values will be imputed using the multiple imputation by chained equations (MACE).^21^ To improve precision of the imputation, the existing qualitative information from Read codes stating the direction of change (eg, ‘weight increasing (1622.00)’) or body mass index (BMI) status (eg, ‘overweight (22AA.00)’) together with other demographic and clinical covariate data will be entered into the imputation regression model.

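### As worded, the plan adjusts the longitudinal weight model for serial TSH, the stated mechanism of the weight change, so the modelled fall and regain would be understated

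*Protocol article*

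**What the plan says.** The Abstract sets a descriptive first aim: "The study will establish the natural history of weight change in hyperthyroidism". Under Outcomes, "The primary outcome is weight change (in kilogram) during and following the treatment for hyperthyroidism". The Data analysis section adds that "The natural history of weight changes will be modelled longitudinally", over a premorbid, a treatment and a post-treatment stage.

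The Confounding section gives the adjustment: "The modelled outcomes will be adjusted for baseline data (sex, age, IMD quartiles, smoking status and comorbidities) and time-varying covariates (thyroid function" and further items. The full time-varying list reads "time-varying covariates (thyroid function, cumulative time on the medical treatment, time since diagnosis, levothyroxine replacement, pregnancy and diagnosis of cancer". Table 2 specifies the thyroid term as "Serial TSH, log-transformed for the analysis".

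On mechanism, the Introduction says that before diagnosis most patients notice that "they lose weight, often despite increased appetite, due to the regulatory effects of thyroid hormones on metabolism". It then links weight change after treatment to the return of hormone levels to normal.

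The text on the natural-history model gives no covariate list of its own. The section on cardiometabolic risks and mortality does give one for its time-varying adjustments: levothyroxine, log TSH and number of GP visits.

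**The concern.** A stage contrast in weight asks how much patients lose before and early in treatment and how much they put back on. In the protocol's own account, thyroid hormone drives that movement, so serial TSH is the pathway of the stage contrast and not a confounder of it. With serial log TSH in the model, each stage coefficient describes weight at a fixed TSH, which is not what patients go through as they pass from one stage to the next.

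The Introduction wants the weight figures for counselling patients about gain during treatment. A fall and regain estimated at constant TSH would be smaller than the change patients experience, and nothing in the article would warn the reader of that.

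**Working it through.** **1. Does the adjustment reach the weight model?** The Confounding section speaks of the modelled outcomes in general. Weight change is the primary outcome and is modelled longitudinally, and no section exempts it. The list is also not just a preview of the event models: it contains pregnancy, cancer and cumulative time on medical treatment, none of which is in the time-varying list for the cardiometabolic and mortality analyses. On the text as it stands, serial log TSH and levothyroxine enter the weight model.

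**2. Is TSH on the pathway?** The Introduction attributes the loss to thyroid hormones and ties later change to their normalisation. Serial TSH therefore carries part of the difference between stages. How large a part is not stated.

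**3. How much would be lost?** The protocol gives no figure to reproduce, so this step is illustrative and every input is assumed: 20,000 patients, three stages, a fall of 5 kg followed by a regain of 5 kg in the reference group, residual SD 2 kg, and a thyroid score with stage means 0, 1 and 0 and within-stage SD 0.3. The model is least squares on stage, with and without the score. A share m of the fall and regain runs through the score.

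The expected result is

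adjusted fall = fall × (1 − m × r),

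where r is the within-stage reliability of the thyroid measure. Without measurement error r = 1. With error SD 0.3, r = 0.3² / (0.3² + 0.3²) = 0.5.

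| Share m | Formula, r = 1 | Simulated fall (kg) | Formula, r = 0.5 | Simulated fall (kg) |
|---|---|---|---|---|
| 0% | 5.00 | 5.01 | 5.00 | 4.94 |
| 25% | 3.75 | 3.77 | 4.38 | 4.36 |
| 50% | 2.50 | 2.49 | 3.75 | 3.74 |
| 75% | 1.25 | 1.22 | 3.13 | 3.08 |
| 100% | 0.00 | −0.07 | 2.50 | 2.54 |

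The regain shrinks in the same way: 4.99, 3.76, 2.51, 1.20 and −0.04 kg without error, and 4.95, 4.35, 3.79, 3.07 and 2.52 kg with it. Without the thyroid score, the fall is 4.95 to 5.03 kg and the regain 4.94 to 5.04 kg in all ten runs.

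**4. Post-treatment minus premorbid (overshoot).** In the reference group this is regain minus fall, set to zero. With the score in the model it stays within 0.05 kg of zero in every run (for example 2.51 − 2.49 = 0.02 at 50%, and 3.79 − 3.74 = 0.05 at 50% with error). The reason is that the score is the same on average before and after. On the log TSH scale, with assumed medians of 1.5, 0.05 and 1.8 mIU/L, the premorbid-to-treatment shift is ln(0.05/1.5) = −3.40 and the premorbid-to-post shift is ln(1.8/1.5) = 0.18, about 5% as large. Under full mediation and error-free TSH, adjustment would then move the overshoot by about 5 × 0.18/3.40 = 0.27 kg, against 5 kg for the fall. This protection depends on TSH returning close to its premorbid level. A group whose TSH stays away from that level would have less of it.

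**The case against.** The strongest reply is about scope. The section is headed Confounding and concerns variables that affect both treatment choice and outcome, so its list may be meant only for the comparison between treatments. Log TSH and levothyroxine are named explicitly only for the cardiometabolic and mortality models, and the covariate roles are to be explored in the data. The causal graph is not visible here, and a condensed article may leave each model's covariates to a fuller document. That makes the reach of the adjustment a reading of general wording, not an explicit TSH term in the stage model. It does not remove the point: the wording is general, nothing overrides it, and exploring associations cannot tell a mediator from a confounder, because TSH would be strongly associated either way.

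Three further replies stand in part. Descriptive summaries of weight are planned, so unadjusted figures will exist, although the article does not say that they are by stage. A TSH-adjusted model could still yield the experienced trajectory if its predictions were averaged over observed TSH, but the plan does not say so. Baseline fT4 is a fair confounder of treatment choice and is not in question; the difficulty is with serial values.

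A reader might infer that the fall and regain would vanish from the results. The documents do not support that. It needs the whole effect to run through TSH and TSH to be measured without error, and the protocol gives no figure for either. Nor can the loss be sized from the 5.4 kg reported in the Introduction for antithyroid drugs: that is a final gain from baseline, including any overshoot, and not a premorbid-to-treatment fall.

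**Conclusion.** The point holds in a limited form. As worded, the plan conditions the longitudinal weight model on serial log TSH, which the protocol presents as the mechanism of the change being described. Stage coefficients at equal TSH would understate the fall and the regain. The direction follows from the text whenever some of the effect runs through TSH. The size depends on the unknown share acting through TSH and on how well TSH is measured. With an assumed 5 kg change, the illustration runs from no loss at 0% to half at 100% with reliability 0.5, and to complete loss only in the extreme case of 100% with error-free TSH.

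The post-treatment minus premorbid contrast, which carries the overshoot question, is little affected where TSH returns near its premorbid level. The point is confined to the within-patient stage contrast. It makes no claim about the treatment comparison in the event models. The wording should be changed before analysis, but it does not undermine the study as a whole.

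**What to change.** In the Confounding section and in the text on the natural history of weight changes, state that the main model of weight by stage or time excludes serial TSH and post-index levothyroxine and keeps the baseline covariates and pregnancy. Alternatively, state that trajectories will be reported after averaging over the observed TSH values. The case for leaving out levothyroxine rests on the same on-pathway reasoning, since Table 2 defines it as following the hypothyroidism that develops after radioiodine or thyroidectomy; it was not simulated.

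A TSH-adjusted weight model can be kept as a secondary analysis, labelled as addressing mechanism. The change needs no new data: it is a wording change and one model with fewer covariates. The downside is that residual variance may rise slightly.
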